## Abstract

**Background:**

The majority of persons with dementia in Sweden reside in their own homes with support from family members. Approximately, 12% of persons with dementia have immigrant background. Within the next 20 years, the number of persons with dementia who are non-ethnic Swedes is said to double. Family caregivers with immigrant backgrounds are noted to receive less support in the community than ethnic Swedes and rate their health status lower than ethnic Swedish peers. The Swedish National Board of Health and Welfare have highlighted the importance of follow-up support for family caregivers with immigrant backgrounds as there is a recognized gap in research and available information tailored to meet the needs of this group.

**Purpose of the study:**

The purpose of the study is to test effectiveness of an mHealth based intervention through which community social workers can improve caregiving competence of non-European immigrant family caregivers of people with dementia living at home in Sweden. The overarching aim is to reduce caregiver burden and depressive symptoms, and improve quality of life.

**Methods:**

A randomized controlled trial (RCT) including wait list control group will be performed consisting of an intervention group (A, *n* = 44) and a wait list control group (B, *n* = 44), totaling a sample size of 88. On completion of the 10-weeks long intervention in the intervention group, the intervention will be delivered to group B. Effect of the intervention will be analyzed between and within groups over time. The content of the educational component of the intervention is inspired by the iSupport manual developed by the World Health Organization. The contents, in the form of a booklet, aims to equip the family caregivers with structured information on understanding dementia as a condition and its management at home, including self-care guidance designed specifically for family caregivers themselves.

**Discussion:**

Similar telephone-delivered intervention studies targeted for family caregivers to persons with dementia are ongoing in Malaysia and will start in India using the same booklet adapted to the local context. These studies will provide evidence on the effectiveness of using digital technologies to deliver support to those who may not be reached or adequately served by the traditional healthcare system.

**Trial registration:**

ISRCTN registry, Registration number ISRCTN64235563.

**Supplementary Information:**

The online version contains supplementary material available at 10.1186/s12877-024-05106-x.

## Background

In Sweden, it is estimated that one in every four persons will be 65 years or above by the year 2040 [1]. As a result of an increased aging population with persons aged 80 years and over, the prevalence of dementia is expected to rise from approximately 150,000 in 2012 to 250,000 people by the year 2050. Most persons with dementia, between 55% and 72%, reside in their own homes [2, 3] with support from family members [4]. In 2018, the number of people living with cognitive diseases (dementia) with immigrant backgrounds in Sweden was estimated at 20,000 and set to double within the next 20 years [5]. According to the national Swedish Dementia Register, 12.4% of the registered persons with dementia have immigrant background [6].

Family caregiving plays a pivotal role in all long-term care systems, this is apparent in areas where formal long-term care services are lacking or absent. It is deemed a cost-efficient way of delaying admissions to residential facilities in high-income countries and facilitates the person receiving care to reside in their own home. During the Covid-19 pandemic, the role of family caregivers became more evident in Sweden [7]. According to the European Commission, an informal caregiver is described as a person who cares for or provides assistance to a person with disabilities without financial reimbursement or formal education in health care [8]. It is often family members who assume the role of informal caregivers and are the main source of support for older persons with complex care requirements [9]. In Sweden, one in five adults provide care for an older family member where informal care is regarded as the main source of care provided [7].

In a study of over 170 family caregivers to persons with dementia in Cyprus, 68% experienced elevated levels of burden (more women than men), with 65% reporting symptoms of depression [10]. In the early stages of the dementia disease trajectory, family caregivers are often not identified as needing support by health and social care professionals despite many experiencing depression, anxiety, and insomnia [11]. The level of care provided can often be beyond the caregiver´s capacity and can result in experiences of burden and mental health disorders [12]. Caregiver competence in caring for older frail persons is related to depression among caregivers. Possibilities exist for supporting caregivers by providing targeted interventions which can enhance their competency and mastery in the field [13]. The impact of caregiving on family life, finances and mental health are key components of family caregiver burden [14]. Family caregiving is diverse and complex by nature with roles evolving over time as the disease progresses with caregivers often unprepared for the role [15].

Almost 20% of the population of Sweden (two million people) have an immigrant background. There has been a rise in immigration to Sweden by 9% over the past ten years. The majority of people come from the Middle East (Syria and Iraq) followed by Finland, Poland, and Iran [16]. There is inequity in care provided to persons with dementia with immigrant background compared to ethnic Swedes in regard to clinical assessment, treatment and health care [17]. Family caregivers with immigrant backgrounds are noted to receive less support in the community in the form of home help, respite care and information than ethnic Swedes. Family caregivers with immigrant background have rated themselves as having lower levels of health than their peers and are living with concerns and challenges in relation their situations [18]. In Sweden in 2012, 1.3 million informal caregivers with one in six aged 60 years and older identified themselves as providing care for their cohabitating partner [19]. The response to this survey among people born outside of Sweden was low. The Swedish National Board of Health and Welfare have highlighted the importance of follow up support for family caregivers with immigrant backgrounds as results of previous studies do not represent this group.

The World Health Organization highlights, in their guidelines for community-based interventions for integrated care for older people, the need to provide support to family and informal caregivers who care for older people [20]. Areas of importance for caregivers are emotional support, help accessing and navigating healthcare systems, support with daily living and managing the situation. In Sweden, research shows the importance of advocating the value of a person-centered approach to meet the specific needs of family caregivers to persons with dementia. This is especially relevant for family caregivers who experience a lack of support in managing behavioral and cognitive symptoms in caring for their family member with dementia. Family caregivers can feel vulnerable and socially isolated in their caring role [21]. According to the Ministry of Health and Social Welfare, the Social Services Act (2001:453) in Sweden states that the municipalities in the country are responsible for providing support services for family caregivers who care for persons with chronic illnesses, persons with function variations and older persons [22]. In Sweden, health and social care workers, e.g. dementia care nurses and social workers supporting family members, work both at regional levels and locally in the municipalities to provide support for families living with dementia. Support offered includes providing information and guidance. Despite this a Swedish study showed that 75% of family caregivers were not aware of the availability of such support [23]. When family caregivers´ needs and wishes for information are unmet [24], availability of information via technology can be one way to strengthen their role and help them make informed decisions.

Mobile health, otherwise known as mHealth, is a form of telehealth and in general terms describes the use of mobile and wireless technology in health care [25]. Mobile phones or tablets are commonly used [26]. The goal of mHealth is to promote delivery, health outcomes and efficiency in health care systems [26]. In a literature review by Zhao et al. [27], factors which contributed to care efficiency while using mHealth included that the applications were user friendly, provided personalized support and allowed accessibility in communicating with health care professionals. Over the last two decades, the availability of interventions to reduce family caregiver burden within health care has increased, however such interventions have mainly been carried out face to face. A rise in the use of information and communication technology (ICT) has opened up for novel possibilities to support family caregivers where geographical distances from services or lack of resources in the community have been viewed as barriers to support. An example of an ICT based intervention supporting family caregivers to persons with dementia is Diapason, a web-based automated educational program [28]. Recent research promotes the need for further development of smartphone based mobile applications focusing on the complex needs of family caregivers in providing support for a person with dementia [29].

## Methods

### Aim

The aim of the randomized controlled trial described in this study protocol is to test effectiveness of an mHealth based intervention through which community social workers can improve caregiving competence of non-European immigrant family caregivers of people with dementia living at home in Sweden. The overarching aim is to reduce caregiver burden and depressive symptoms, and improve quality of life.

### Research questions

Is mHealth-based intervention delivered by community social workers effective in reducing caregiver burden and depressive symptoms of non-European immigrant family caregivers to people with dementia living at home?Is mHealth-based intervention delivered by community social workers effective in improving quality of life of non-European immigrant family caregivers to people with dementia living at home?

### Study design

This randomized controlled trial (RCT) will include a wait list control group. Participants will be randomly assigned to the intervention group and the wait list control group. On completion of the 10-weeks long intervention in the intervention group (Group A), the intervention will be delivered to the wait list control group (Group B). Effect of the intervention will be analyzed between and within groups over time.

### Definitions

Family caregiver of Person with Dementia (PWD) is defined as one who provides informal care, hereupon referred to as ***family caregivers***.

### Community workers

The term community workers indicate Social Care Professionals (SCP) based in municipalities in Sweden. They include professionals, i.e., social workers, Silvia Nurses (specially trained in dementia care) and dementia coordinators providing support to family caregivers of people with dementia. SCPs in the selected municipalities will select family caregivers through their own network in their catchment area.

### Study sites

The research will be conducted in partnership with SCPs in municipalities with high immigrant density in Stockholm County (and other counties if the required sample size is not reached) in Sweden.

### Study participants and inclusion criteria

Participants in the RCT will include (i) family caregivers of PWD living at home. The family caregivers are the recipients of the intervention. In the case of more than one family caregiver for a PWD, they will be included either in the same intervention or the same wait list control group; and (ii) SCPs who will deliver the intervention. Inclusion criteria of family caregivers are adults of non-European immigrant background in Sweden, who have provided care to a PWD living at home for at least six months, possess a smartphone or tablet, has access to the internet at his/her own cost, and able to read and write Swedish. Family caregivers aged under 18 years, and/or those suffering from conditions that impede communication will not be included in the study.

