### Recruitment of participants

#### Quantitative component

Sample size calculation of family caregivers is based on the primary outcome caregiver burden assessed by Zarit Burden Interview [30]. Assuming an effect size of 0.70, alpha 0.05, power 0.80, and 25% refusal or drop-out rate, the required sample size will be 44 family caregivers each in intervention group and wait list control group, totaling a sample size of 88. Recruitment of family caregivers will be done in multiple ways. The SCPs of the municipalities selected for the study will announce to all in the network of the family caregivers of PWD, as defined above, who are in their catchment area. Announcement about the project and invitation to join the study will be published in the local newspaper if necessary. Cultural and community organizations of different ethnic minority groups will also be reached out with information on the project. Participants will be randomized 1:1. To ensure allocation concealment, a sealed opaque envelope containing 88 small pieces of paper with numbers 1–88 written on it. Of these, 44 will be marked with “I” to indicate intervention group and another 44 with “C” to indicate control group. Once a participant is enrolled in the study, a person outside the research group will randomly pick a piece of paper from the envelope to indicate if the enrolled participant will belong to the intervention group or the wait list control group.

After inclusion, the SCP will contact a designated member of the research team who will draw a sealed envelope which will decide the allocation to either control or intervention group. A SCP selected for the study will be responsible for 5–7 family caregivers at a time for delivering the intervention. Those family caregivers not selected in the initial intervention group, i.e., those in the wait list control group, will continue to receive the standard support. Recruitment of study participants is expected to begin in August 2024.

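### Co-caregivers of one person with dementia must share an arm, but the allocation procedure draws a slip per participant, gives no rule for them, and the sample size makes no allowance for the pairing

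*Protocol article*

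**What the plan says.** Under *Study participants and inclusion criteria*, the protocol article provides for a person with dementia who has more than one family caregiver in the trial: "they will be included either in the same intervention or the same wait list control group".

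Under *Recruitment of participants, Quantitative component*, allocation is by individual: "Participants will be randomized 1:1". The envelope holds 88 numbered slips: "Of these, 44 will be marked with “I” to indicate intervention group and another 44 with “C” to indicate control group". After enrolment, "a person outside the research group will randomly pick a piece of paper from the envelope to indicate if the enrolled participant will belong" to one group or the other. Nothing is said about a second caregiver of the same person.

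The sample size in that section is counted in caregivers. The inputs are "Assuming an effect size of 0.70, alpha 0.05, power 0.80, and 25% refusal or drop-out rate", and the result is that "the required sample size will be 44 family caregivers each in intervention group and wait list control group, totaling a sample size of 88". No allowance for correlated participants is listed.

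Under *Data analysis, Outcome analysis*, the article states that participants, social care professionals and researchers cannot be blinded. The method named there is regression, with no error structure given.

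**The concern.** The two sections use different units. The inclusion section allocates the group of caregivers around one person with dementia. The recruitment section allocates each caregiver. A site that enrols two siblings caring for one parent cannot tell from the text whether to draw once, draw twice and override the second slip, or draw once and set a second slip aside.

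Two things are at stake.

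- **Concealment.** Suppose the second caregiver comes forward after the first has been allocated. The arm is then fixed by the same-arm rule and is known to the family and to the professional who recruits and delivers the intervention. One arm starts at once and the other waits until the first group has finished its 10 weeks, so willingness to join may depend on the arm. That would be selection after randomisation, acting on a self-reported burden score, and no analysis model reliably removes it.
- **Precision.** Two people rating the strain of the same care situation are likely to give correlated scores. When both are always in one arm, the correlation inflates the variance of the arm mean. A sample size that omits it overstates power.

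**Working it through.** **1. Reproduce the stated sample size.** Inputs from the recruitment section: d = 0.70, alpha 0.05, power 0.80, 25% loss. Sidedness is not stated; two-sided is taken because it reproduces the figure.

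- Normal formula per arm: 2(1.960 + 0.842)² / 0.70² = 32.04, rounded up to 33.
- Allowing for loss: 33 / 0.75 = 44 per arm, 88 in total. This matches exactly.
- Alternatives: the t-test version gives 34, then 46; one-sided gives 26, then 35.

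The stated figure is therefore the independent-observations figure, with a design effect of 1.

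**2. Can individual draws honour the same-arm rule?** After one slip is drawn, 87 remain, of which 44 carry the other letter. The chance that two co-caregivers drawing separately land in different arms is 44/87 = 0.51. Because slips are drawn without replacement, this holds for any two positions in the sequence. If the second draw is skipped and no slip is set aside, each pair leaves one slip unused and the caregiver totals are no longer held at 44 and 44.

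**3. Effect of pairing on precision.** Let q be the share of participants who belong to a pair and ρ the correlation of burden scores within a pair. Each paired participant adds one covariance term to the variance of the arm mean, so the design effect is DE = 1 + qρ. The article gives neither q nor ρ; the values below are assumptions. Power uses the 33 evaluable per arm as 33/DE in a noncentral t with 64 degrees of freedom and d = 0.70. With DE = 1 this gives 0.80. The last column is the true two-sided error of a test that ignores pairing, 2[1 − Φ(1.96/√DE)].

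| q | ρ | DE | 33/DE | Power | Type I if pairing is ignored |
|---|---|---|---|---|---|
| 0.10 | 0.3 | 1.03 | 32.0 | 0.79 | 5.3% |
| 0.20 | 0.5 | 1.10 | 30.0 | 0.76 | 6.2% |
| 0.40 | 0.7 | 1.28 | 25.8 | 0.70 | 8.3% |

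**4. Sample size with the design effect.** Take 32.04 × DE, round up, divide by 0.75 and round up:

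- DE 1.03: 33.0, so 33, then 44 per arm.
- DE 1.10: 35.2, so 36, then 48 per arm.
- DE 1.28: 41.01, so 42, then 56 per arm.

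At the low end the rounding in the original calculation absorbs the clustering. Ten per cent of 88 is about four pairs; 40% is about 18.

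**The case against.** The strongest reply is that the same-arm sentence is a special case within a general 1:1 scheme. One slip could serve the caregiver group, with a slip of the same letter removed for each further co-caregiver. That keeps both the same-arm rule and the 44/44 total, and a condensed article may leave such a step to the full protocol. This stands in part: a reader might infer that the two sections can never be reconciled, and that is too strong. But the recruitment section describes the mechanism down to the marks on the slips, and as described it does not carry out the same-arm rule. An analysis plan written later cannot repair allocations already made.

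Three further limits stand.

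- A reader might infer that a second caregiver's arm is always known in advance. The article does not say whether co-caregivers enrol together or in sequence. If all enrol before a single draw, concealment is intact. The weakness is that nothing requires this.
- A reader might infer that the analysis will ignore pairing and that type I error is inflated. The article commits to regression without an error structure, and an analysis plan that is not shown may handle clustering. Independence is demonstrated for the sample size only.
- Pairs may be few. Each co-caregiver must separately meet all the inclusion criteria, including reading and writing Swedish, and nothing in the article suggests that pairs are common.

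The relevant cluster is the person with dementia, not the household: co-caregivers may live apart.

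**Conclusion.** The point holds. The same-arm rule and the per-participant draw use different units, and the article gives no rule that joins them. This is certain from the text, and it matters because concealed allocation carries much of the weight in a trial that cannot be blinded.

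The loss of concealment is conditional on a co-caregiver enrolling after the first draw. The article permits that sequence but does not state it.

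The sample size treats caregivers as independent; the exact match at 33/0.75 = 44 shows this. Under the assumed 10–40% in pairs and correlation of 0.3–0.7, power is about 0.79–0.70 instead of 0.80, which is negligible at the low end and material only if pairs are common. The 5.3–8.3% type I error applies only to an analysis that ignores pairing, and the article does not settle whether it will.

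**What to change.** - **Unit.** State that the person with dementia, meaning the group of participating caregivers around that person, is the unit of randomisation.
- **Order.** Identify, consent and take T1 from all participating co-caregivers first, then make a single draw. Add no caregiver of that person to the trial data after the draw.
- **Slips.** Say how they are used. Either remove one slip of the same letter for each further co-caregiver, with a provision for when none is left, or use one slip per person with dementia and accept slightly unequal caregiver numbers.
- **Analysis.** Use a random intercept for, or standard errors clustered by, the person with dementia.
- **Power.** Restate it with a design effect, giving the assumed share of pairs and correlation.

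The cost is some protocol wording and one model term. Caregiver numbers may not come out at exactly 44 and 44, and the stated power becomes slightly lower. The allocation wording should be settled before any co-caregiver is allocated.

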### Recruitment of participants

#### Quantitative component

Sample size calculation of family caregivers is based on the primary outcome caregiver burden assessed by Zarit Burden Interview [30]. Assuming an effect size of 0.70, alpha 0.05, power 0.80, and 25% refusal or drop-out rate, the required sample size will be 44 family caregivers each in intervention group and wait list control group, totaling a sample size of 88. Recruitment of family caregivers will be done in multiple ways. The SCPs of the municipalities selected for the study will announce to all in the network of the family caregivers of PWD, as defined above, who are in their catchment area. Announcement about the project and invitation to join the study will be published in the local newspaper if necessary. Cultural and community organizations of different ethnic minority groups will also be reached out with information on the project. Participants will be randomized 1:1. To ensure allocation concealment, a sealed opaque envelope containing 88 small pieces of paper with numbers 1–88 written on it. Of these, 44 will be marked with “I” to indicate intervention group and another 44 with “C” to indicate control group. Once a participant is enrolled in the study, a person outside the research group will randomly pick a piece of paper from the envelope to indicate if the enrolled participant will belong to the intervention group or the wait list control group.

After inclusion, the SCP will contact a designated member of the research team who will draw a sealed envelope which will decide the allocation to either control or intervention group. A SCP selected for the study will be responsible for 5–7 family caregivers at a time for delivering the intervention. Those family caregivers not selected in the initial intervention group, i.e., those in the wait list control group, will continue to receive the standard support. Recruitment of study participants is expected to begin in August 2024.

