#### Educational component of the intervention

The educational component of the intervention will be delivered by SCPs in Sweden via a mobile app. The intervention will be delivered in 10 sessions with specific topics for each session and which is based on World Health Organization’s recommendation of support for family caregivers. The topics include an introduction to dementia, being a caregiver, mental strategies and mind-set, activities, diet and sleep, and where to find resources in the community. The family caregiver will receive a booklet, presenting each topic and a minor task which will be followed up in the next session with the SCP. One of the 10 sessions will be kept as an open choice allowing the family caregiver to freely address any topic pertinent to their unique situation. The content of the intervention will be refined based on consultative workshops with stakeholders including SCPs, immigrant family caregivers of PWD, older persons of immigrant background and experts.

In addition to SCPs delivering the intervention through the chat feature on a mobile application, other features of the app will include:

***Interaction with community workers***: Using the chat feature, family caregivers will be able to communicate directly with the SCPs on a one-on-one basis throughout the 10-week intervention period.***Relevant services***: Collection of weblinks of relevant services in their communities will be available.***Peer support***: The family caregivers will be able to chat with their peers, i.e., other family caregivers of persons with dementia, at the time of their preference.***Wellbeing***: Mindfulness exercises will be available for the family caregivers.***Diary***: The family caregivers will be able to write down personal notes and reflections.

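### The sample size makes no allowance for caregivers who share an SCP or a household, so the stated 0.80 power holds only if those correlations are zero

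*Protocol article*

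**What the plan says.** All places are in the protocol article.

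- **Sample size** (Recruitment of participants, Quantitative component): "Sample size calculation of family caregivers is based on the primary outcome caregiver burden assessed by Zarit Burden Interview". The inputs are "Assuming an effect size of 0.70, alpha 0.05, power 0.80, and 25% refusal or drop-out rate", which lead to 44 per arm and 88 in total. No ICC, design effect or number of SCPs is mentioned.
- **Allocation** (same section): "Participants will be randomized 1:1", by drawing from one envelope of 88 papers, with no strata.
- **Delivery** (same section): "A SCP selected for the study will be responsible for 5–7 family caregivers at a time for delivering the intervention". The wait-list arm has standard support until its own turn.
- **Households** (Study participants and inclusion criteria): when one person with dementia has more than one caregiver, all of them go to the same arm.
- **Contact** (Educational component of the intervention): SCP contact is one-on-one chat over 10 weeks, and there is also a peer chat.
- **Analysis** (Outcome analysis): regression analyses are named. SCP is neither included nor excluded as a model term.

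**The concern.** Caregivers treated by the same SCP share that SCP's skill, style and diligence, so their outcomes may be correlated even when every contact is individual. The training section plans meetings at which SCPs calibrate their approach, so the authors themselves expect some variation between SCPs. Up to T2 this correlation arises in the intervention arm only. Co-caregivers of one person with dementia are a second source, possible in both arms.

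Positive correlation makes the variance of the arm mean larger than the sample size formula assumes. With about 6 to 9 SCP groups for 44 caregivers (44/7 = 6.3; 44/5 = 8.8), one unusually strong or weak SCP can move the arm mean. At stake are the power quoted for the trial and, if the final model leaves SCP out, the error rate of the main test.

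**Working it through.** **1. Reproduce the stated figure.** Inputs from the sample size paragraph: d = 0.70, alpha 0.05 (taken as two-sided), power 0.80, loss 25%.

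n per arm = 2 × (1.96 + 0.8416)² / 0.70² = 32.04, rounded up to 33. Then 33 / 0.75 = 44, an exact match. One-sided alpha gives 26 before loss and does not match. With 33 analysed per arm and independent observations, power is 0.80 by the t-test (0.81 by the normal approximation). Nothing is held back for clustering.

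**2. Add SCP clustering in the intervention arm only.** The ICC is an assumption, 0.01–0.10. With m analysed caregivers per SCP:

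- design effect DE = 1 + (m − 1) × ICC
- SE = √(DE/33 + 1/33), noncentrality = 0.70 / SE
- power from the noncentral t with 64 df, or with Satterthwaite df based on k = 33/m SCP groups
- if SCP is omitted from the model: the true SE is r = √((DE + 1)/2) times the naive SE, and type I error = 2 × (1 − Φ(1.96/r))

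If the 25% is lost after assignment, 5–7 per SCP become 3.75–5.25 analysed and the number of SCPs stays at 44/7 to 44/5.

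Middle case (6 assigned, 4.5 analysed, ICC 0.05): DE = 1 + 3.5 × 0.05 = 1.175; SE = √(2.175/33) = 0.257; noncentrality = 0.70/0.257 = 2.73. Power is 0.77 with 64 df and 0.735 with about 19 df.

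| Analysed per SCP | SCP groups | ICC | DE | Power, 64 df | Power, small-sample df | Type I error if SCP omitted |
|---|---|---|---|---|---|---|
| 3.75 | 8.8 | 0.01 | 1.03 | 0.79 | 0.77 | 5.2% |
| 3.75 | 8.8 | 0.10 | 1.275 | 0.75 | 0.72 | 6.6% |
| 4.5 | 7.3 | 0.05 | 1.175 | 0.77 | 0.735 | 6.0% |
| 5.25 | 6.3 | 0.10 | 1.425 | 0.72 | 0.67 | 7.5% |
| 7 (no shrinkage) | 4.7 | 0.10 | 1.60 | 0.69 | 0.61 | 8.6% |

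Part of the small-sample loss is the price of having few SCPs: at ICC 0 that column would already read 0.78 (8.8 groups) to 0.77 (6.3 groups).

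The last row applies if the 25% is mainly refusal before assignment, so that groups stay full. The wording "25% refusal or drop-out rate" allows either reading. If an SCP serves two intervention-arm cycles, the analysed group could reach 2 × 7 × 0.75 = 10.5, and power with 64 df falls to 0.71 at ICC 0.05 and 0.64 at ICC 0.10.

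**3. Effect of adjusting for T1.** With T1–T2 correlation r, the variance is multiplied by 1 − r², taking the same ICC on the adjusted scale. r is an assumption. For 3.75–5.25 analysed per SCP and small-sample df:

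- r = 0.5 (factor 0.75): power is 0.88 at the favourable end and 0.79 at the unfavourable end (5.25 per SCP, ICC 0.10). With full groups of 7 and ICC 0.10 it is 0.73.
- r = 0.3 (factor 0.91): 0.81 down to 0.71.

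**4. Households.** The article gives no frequency of co-caregivers, so no figure is put on this. A positive household correlation would lower power further.

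All power figures refer to the comparison of means that underlies the sample size, not to an analysis of the odds of improvement.

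**The case against.** Four points on the other side have weight.

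- **The ICC is unknown and may be small.** Contact is one-on-one, all SCPs follow one 10-session booklet, and calibration meetings are meant to align them. At ICC 0.01–0.02 the loss is about 1–2 points before the df penalty. A reader might infer that 0.80 power is definitely not delivered. The article supports less: there is no margin, and the loss ranges from negligible to material.
- **The analysis model is not described.** A reader might infer that the analysis treats the intervention arm as independent and that its intervals are too narrow. The article says only that regression will be used. A model with an SCP effect is still a regression, and such terms may stand in a full protocol or SAP that is not shown. The type I error figures are therefore conditional on SCP being omitted.
- **The peer chat is not tied to SCP groups.** The text is "The family caregivers will be able to chat with their peers, i.e., other family caregivers of persons with dementia", with no statement that chat partners share an SCP. It cannot be counted as a source of clustering within SCP, and the case does not need it.
- **Group size should be counted after loss.** Pairing 33 analysed caregivers with full groups of 5–7 overstates the effect if loss follows assignment. The main figures above therefore use 3.75–5.25, and the full-group figures are shown only as the unfavourable case.

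None of this removes the central fact: the stated number reproduces exactly under independence, in the same section that describes shared delivery.

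**Conclusion.** The point holds for the sample size. The 44 per arm assumes independent caregivers, and the design described beside it does not make them independent. The t-test power is 0.80 only at zero correlation. Under an assumed within-SCP ICC of 0.01–0.10 and loss after assignment, it is about 0.79–0.72 (0.77–0.67 with small-sample df), with a middle case of 0.77 (about 0.74). It is lower if groups stay full or SCPs serve several intervention-arm cycles, with 0.69 (0.61) for full groups of 7 at ICC 0.10. An inflated type I error, about 5.2–7.5% and up to 8.6% with full groups, follows only if the final model leaves SCP out. This should be corrected, but it does not threaten the trial, because the T1 score already planned can offset much or all of the loss.

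**What to change.** - In the sample size paragraph, replace the single power of 0.80 by power over a stated ICC range, with the expected number of SCPs and whether an SCP may serve more than one intervention-arm cycle.
- Record the SCP identifier and a household identifier from enrolment.
- State, in the article's analysis section or the SAP, that T2 burden is analysed with a partially nested mixed model: SCP random effect in the intervention arm only, small-sample df, allowance for co-caregivers of the same person with dementia, and adjustment for T1 burden. If the SAP already says this, a cross-reference is enough.
- Do not describe SCP or municipality as a randomisation stratum. The single-envelope draw is unstratified, and no study SCP is documented for wait-list caregivers before T2.

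The cost is two recorded identifiers, a few model terms, slightly wider intervals than a model without SCP would give, and a less favourable stated power. More participants are not needed if the T1–T2 correlation is near 0.5 and analysed groups are 3.75–5.25 per SCP. At 0.3, the offset is only partial at the higher ICCs.
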